# Aerobic exercise as a therapeutic intervention for post-traumatic stress disorder in women who have experienced intimate partner violence: study protocol for an open-label randomised controlled trial

**DOI:** 10.1186/s13063-026-09796-z

**Published:** 2026-05-29

**Keywords:** Exercise, Intimate partner violence, Post-traumatic stress disorder, Domestic and family violence

## Abstract

**Background:**

Women with a history of intimate partner violence (IPV) are at risk for post-traumatic stress disorder (PTSD). The effectiveness of aerobic exercise in reducing PTSD symptom burden has been established in other patient populations; however, its utility in the context of IPV victim-survivors has received little investigation. Therefore, the primary aim of this study is to determine if 4 weeks of daily structured aerobic exercise compared to daily stretching can reduce PTSD symptom burden in women IPV victim-survivors, offering a potential accessible and self-directed treatment avenue.

**Methods:**

The target sample size of 120 women (aged 18–70) with a history of IPV (last instance > 3 months ago) and probable PTSD (via the PTSD Checklist for DSM-5; PCL-5) will be recruited via community advertisement in Melbourne, Australia. The trial will be completed at the Alfred Centre, Monash University. Participants will complete an exercise tolerance test via the Buffalo Concussion Bike Test and then will be randomised into either aerobic exercise or passive stretching. Participants will be instructed to complete 20 min of allocated aerobic exercise or stretching for 4 weeks and given a written diary and a Fitbit smartwatch to track program adherence. The primary outcome, PTSD symptoms via the PCL-5, will be collected at baseline, 1, 2, 3, and 4 weeks (primary endpoint). Secondary outcomes, including additional determinants of health (i.e. sleep, pain, substance use), cognitive testing, concussion-like symptoms in participants with a history of IPV-related brain injury, blood-based biomarkers, and feasibility and adherence to the prescribed program, will also be collected weekly at baseline, 1-, 2-, 3-, and 4-week follow-ups.

**Discussion:**

This trial is an open-label randomised controlled trial to compare the effectiveness of a structured aerobic exercise program to passive stretching in women victim-survivors of IPV with probable PTSD. Results from this trial will help guide the development of individualised, financially accessible, and self-directed care plans for women living with PTSD and other persisting mental and physical health impacts of IPV.

**Trial registration:**

ACTRN12624000893505. Trial registered retrospectively. Registered on 22/07/2024. https://anzctr.org.au/Trial/Registration/TrialReview.aspx?ACTRN=12624000893505

**Supplementary Information:**

The online version contains supplementary material available at 10.1186/s13063-026-09796-z.

## Background

Intimate partner violence (IPV) is a major worldwide healthcare burden that disproportionately affects women. It refers to behaviours by a current or former partner (formal or informal) that cause physical, sexual, or psychological harm and encompasses physical aggression, psychological abuse, and controlling behaviours [1]. Global prevalence of physical and/or sexual violence across a lifetime is 27% [2]. However, meta-analysis suggests that lifetime incidence is significantly increased when also considering psychological IPV, and has been reported up to 37.3% in women aged 16 and over [3].

Persistent mental health conditions are a significant and ongoing challenge for IPV victim-survivors, with post-traumatic stress disorder (PTSD) being one of the most prevalent. PTSD affects an estimated 63.8% of survivors, irrespective of the type of IPV experienced [4]. It is defined as the re-experiencing of a traumatic event in addition to avoidance, negative cognition and mood, alterations in arousal and reactivity affecting functioning for longer than 1 month [5]. PTSD has profound consequences for quality of life, health, and productivity, impacting patients’ families, friends, and employers [6]. Consequently, there is a pressing clinical imperative to identify cost-effective and accessible therapeutics to improve health outcomes among this vulnerable population [7, 8]. This research aims to determine whether aerobic exercise can improve outcomes and quality of life in survivors of IPV with PTSD.

Physical activity has been suggested to improve PTSD symptomology in other populations with high rates of gendered violence [9–11]. Existing research has focused on military populations [12, 13], which disproportionally focuses on male combat-related trauma and may not be generalisable to the PTSD experience in women who have experienced IPV [14, 15]. Where female veterans with PTSD have been the focus, 12 weeks of moderate-intensity aerobic exercise (i.e. brisk walking; 4× per week) was shown to improve PTSD and depressive symptoms using a within-subject design [16]. Interestingly, this population included patients with military sexual assault (50%), military combat-related trauma (27%), and 14% IPV-related PTSD [16]. The beneficial effects of aerobic exercise are believed to occur through mechanisms of enhanced neuroplasticity, reduced inflammation, and regulation of the hypothalamic-pituitary-adrenal axis [9]. Improvements attributed to these mechanisms, such as increases in brain-derived neurotrophic factor (BDNF) protein expression [17] and decreased concentrations of pro-inflammatory cytokines [18, 19], have been demonstrated in rodent models of PTSD and in humans that performed aerobic exercise [17]. However, there is a paucity of research related to the efficacy and mechanisms of aerobic exercise within the context of IPV survivors with PTSD. Therefore, randomised clinical trials are required to strengthen the evidence of aerobic exercise for PTSD among this population [9].

Here, we will investigate the benefit of 4 weeks of structured aerobic exercise interventions on PTSD symptomology, in comparison to control intervention of a program of passive stretching. In addition, we will also assess whether cognition and other biopsychosocial measures are influenced by the intervention. Blood biomarkers related to inflammation and growth factors will be measured to provide mechanistic insights.

### Objectives

The primary objective is to determine the effects of a 4-week program of structured aerobic exercise on PTSD symptom burden in women IPV victim-survivors compared to those who complete a program of 4 weeks of passive stretching. The secondary objective is to determine the effects of the exercise intervention on biopsychosocial measures (i.e. quality of life, depression, anxiety and stress, concussion-like symptoms, sleep), cognitive performance, and blood biomarkers related to inflammation and growth factors compared to passive stretching.

## Methods

### Design

This trial is an open-label randomised controlled superiority trial to compare the effectiveness of aerobic exercise to passive stretching in women victim-survivors of IPV with probable PTSD. Trial design is such that participants will be randomly allocated using simple randomisation (ratio 1:1) in parallel to either aerobic exercise intervention or control passive stretching intervention. This trial will be taking place at the Alfred Centre at Monash University in Melbourne, Australia. No patients or members of the public were involved in the design, conduct, or reporting of this protocol due to the sensitive nature of the study population.

### Population

Women aged 18–70 with a history of IPV (last instance > 3 months ago) and probable PTSD (via the PTSD Checklist for DSM-5; PCL-5) will be recruited.

### Inclusion criteria

Women aged between 18 and 70 yearsSelf-report history of IPV, with the last occurrence being at least 3 months priorProbable PTSD as measured by a score of >31 on the post-traumatic stress disorder checklist for DSM-5 (PCL-5)Have daily access to a smartphone and the internet

### Exclusion criteria

Subjects who are not willing or able to exercise due to health or personal reasons (e.g. orthopaedic injury, cervical spine injury, diabetes, known heart disease, or musculoskeletal injuries which could make exercise difficult or painful) via the Physical Activity Readiness Questionnaire (PAR-Q)Increased cardiac risk indicated by two or more of the following:Prior diagnosis of, or currently taking medication for cardiovascular (e.g. beta-blockers), metabolic, or pulmonary conditionsFamily history of myocardial infarction, coronary revascularisation, or sudden death before 55 yearsDiagnosis of hypertensionDiagnosis of hyperlipidaemiaSubjects with peripheral circulatory disordersHistory of prior head injury as defined by:Any head injury within the last 30 daysModerate or severe TBI, defined as a brain injury with an associated Glasgow Coma Scale score of 12 or lessDiagnosis of a neurological disorder (e.g. stroke, multiple sclerosis, epilepsy, brain tumour/cancer, encephalitis, dementia, movement disorder, spontaneous nystagmus, or brain surgery)History of drug or alcohol dependency or abuse within a year before screening by self-reportLimited English proficiency precluding completion of measuresSignificant psychiatric history (e.g. psychiatric hospitalisation, schizophrenia, history of legal trouble for violence)IPV history < 3 monthsNo PTSD symptomology at the initial visit (i.e. asymptomatic)Sustaining a head injury during the research periodNew (<1 month) or non-stable or pharmacological regimen prior to intervention (regimen must be maintained for the duration of intervention)Exercise-tolerant individuals with a current activity level equal to or greater than the proposed intervention as indicated by modified Godin Leisure-Time Exercise

### Study outline

The trial will encompass a total of 5 sessions over 4 weeks. Participants with low exercise risk will meet a researcher in person at the Alfred Centre for baseline and subsequent weekly follow-up assessments thereafter. Daily exercise or stretching will be performed by the participants at their own discretion. A flowchart of the study timeline is provided in Fig. 1.

**Fig. 1 Fig1:**
[figure not shown]
Study timeline flowchart

### Sample size

Although there are limited studies to base a statistical power calculation, the sample size was determined based on previous sample size estimates from trials using sub-symptom threshold aerobic exercise (STAE) interventions, which ranged from 46 to 96 participants [20, 21]. With an estimated drop-out rate of 20%, we will aim to recruit 120 participants [21].

### Recruitment and screening process

Potential participants will be recruited through advertisement flyers in the community (e.g. hospitals, libraries, sports centres, women’s health and family violence services, community hubs, and rehabilitation clinics), social media, and by contacting participants from ongoing projects. When an individual provides consent to be contacted, a staff member on the research team will conduct a phone call to determine eligibility. During the phone call, participants will be assessed based on the inclusion and exclusion criteria. This will include PTSD symptoms, estimates of physical activity (i.e. Godin Leisure-Time Exercise) [22], cardiac risk, and individual safety in engaging in exercise (i.e. The Physical Activity Readiness Questionnaire; PAR-Q) [23].

### Informed consent

At baseline, participants will be given a verbal summary of the study as well as any potential risks associated with participating. Participants were also given a list of mental health and IPV resources to contact if any aspect of the trial triggers distressing thoughts or feelings. Before commencing baseline surveys, participants will be given written informed consent.

## Interventions

### Aerobic exercise intervention

Participants determined to be exercise tolerant will be instructed to complete 4 weeks [24, 25] of aerobic exercise at the prescribed target heart rate (HR) of 50–65% of age-predicted HR [26, 27]. Participants determined to be exercise intolerant via the Buffalo Concussion Bike Test (BCBT) will be instructed to complete 4 weeks of STAE. The STAE prescription target HR will be 80% of the HR achieved at symptom exacerbation on the BCBT at the most recent visit. All participants will be required to complete 20 min of aerobic exercise of choice at home or in a gym at the individually prescribed HR, monitored by wearing a provided HR tracker (Fitbit Inspire 3). Participants performing STAE will be instructed to stop their exercise session if their symptoms increase by two or more points from their pre-exercise symptom level (on a 10-point Visual Analog Scale) or at 20 min, whichever comes first. All participants will be encouraged to perform 5 min of chosen warm-up and cool down. They will be told to rest apart from the prescribed exercise and not participate in other physically engaging activities. A 4-week intervention was chosen to align with the interventions’ previous interventions using aerobic exercise as a therapeutic intervention for brain injury [24, 25].$$Max\;Heart\;Rate\;=\;210\;-\;0.79\lbrack Current\;Age\rbrack$$$$\begin{array}{c}Goal\;heart\;rate\;=\;(Max\;Heart\;Rate\;-\;Resting\;Heart\;Rate)\;x\;Goal\;Percent\;Effort\;+\\Resting\;Heart\;Rate.\end{array}$$$$\begin{array}{c}\mathrm{Example}:\;45-\mathrm{year}-\mathrm{old}\;\mathrm{woman},\;\mathrm{resting}\;\mathrm{heart}\;\mathrm{rate}\;50\mathrm{bpm},\;\mathrm{goal}\;\mathrm{percent}\;\mathrm{effort}\;60\%\\210\;-\;0.79(45)\;=\;174\\(174-50)\;x\;0.60+50=124+/-10\mathrm{bpm}\end{array}$$

### Placebo stretching intervention

Participants assigned to the control passive stretching group will be instructed to follow a prescribed stretching program. This group will be provided with a booklet containing a gentle, whole-body, progressive stretching program (with pictures and instructions) that does not considerably elevate HR to perform for 20 min per day for 4 weeks. Participants will be asked to return weekly to re-evaluate performance on the BCBT. All participants will be encouraged to perform 5 min of chosen warm-up and cool down. They will be told to rest apart from the prescribed exercise and not participate in other physically engaging activities. Following 4 weeks of passive stretching intervention, participants will be re-evaluated for exercise intolerance and offered the option to participate in the 4-week aerobic exercise intervention.

## Outcomes

### Primary outcome

The primary outcome of this trial is PTSD symptom burden measured by the PTSD Checklist for DMS-5 (PCL-5) (Table 1). The PCL-5 is a validated and reliable survey for measuring severity of PTSD symptoms and has been used to measure symptom burden in IPV victim-survivors in previous studies [28–30]. The PCL-5 is composed of 20 questions to determine how much a participant was bothered by common PTSD symptoms in the past 3 months. Each question/symptom is ranked on a five-point Likert scale from “0”—not at all to “4”—extremely, with the highest possible value being 80. Probable PTSD was described as a PCL-5 score of >31.

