## Data collection, management, and analysis

### Trial allocation

This study is an open-label study; therefore, the investigator, site staff, and subjects will not be blinded to treatment allocation. A computer-generated randomisation schedule will be prepared by a statistician prior to the start of the study. Treatment allocation will be made per the randomisation list. After signing the informed consent form, subjects will be allocated a unique subject ID and administered the screening instruments via Research Electronic Data Capture (REDCap). A unique subject ID will be used to identify the subject throughout the study period and on all study-related documentation. After eligibility has been established, subjects will complete all baseline assessments followed by a simple randomisation in a 1:1 ratio to either the aerobic exercise or stretching group. Randomisation will be allocated sequentially based on the pre-determined randomisation schedule and according to their chronological order of inclusion in the study.

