### Assessment and collection of outcomes

Participants will be assessed at baseline (day 0) and at the primary endpoint (day 28). During the trial, participants will return and be re-evaluated weekly on PTSD symptoms, BCBT, biopsychosocial questionnaires, and fluid biomarkers. In addition to exercise compliance, medications, and therapies, as well as any adverse events, compliance and feasibility will be evaluated at the weekly follow-up appointment. Cognitive assessment will only be repeated on the final evaluation. All data collection will occur at the Alfred Centre, Monash University. The full study schedule is included (Table 2).

**Table 2 Tab2:** Study schedule

Study assessments	Screening	Baseline	Intervention period	Weekly follow-up	Final visit
		Day 0	Day 1–6; day 8–13; day 15–20; day 22–27	Day 7, 14, 21	Day 28
Screening					
Eligibility questionnaire	X				
Enrolment					
Inclusion/exclusion criteria review	X	X			
Informed consent		X			
Allocate unique subject study identification		X			
Questionnaires					
Demographic data		X			
Medical history		X			
Ohio State University TBI Identification Method		X			
Godin Leisure-Time Exercise questionnaire		X		X	X
Medications		X		X	X
Current therapies		X		X	X
Exercise tolerance test					
Buffalo Concussion Bike Test (BCBT)		X		X	X
ECG recording		X		X	X
Biopsychosocial					
PTSD symptomology: PCL-5	X	X		X	X
Rivermead Post-Concussion Symptoms Questionnaire (RPQ)		X		X	X
Depression, Anxiety & Stress Symptom Scale (DASS-12)		X		X	X
The Alcohol, Smoking and Substance Involvement Screening Test (ASSIST-LITE)		X			X
Brief Pain Inventory (BPI)		X			X
12-Item Short Form Health Survey (SF-12)		X			X
World Health Organisation Quality of Life (WHOQOL-BREF)		X			X
Sleep-related inventory (SRI)		X			X
International Trauma Questionnaire (ITQ)		X			X
Neuropsychological assessment					
TOPF		X			
RAVLT		X			X
Digit Span		X			X
O-SDMT		X			X
TMT		X			X
Biomarkers					
Blood sample collection		X		X	X
Therapeutic intervention					
Dispense intervention		X		X	
Fitbit—dispense and instructions		X			
Record daily intervention sessions			X		
Return of Fitbit					X
Safety and feasibility assessments					
Adverse event monitoring		X		X	X
Feasibility					X

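### The primary outcome is described with a 3-month recall period but is scored weekly and compared at day 28; if it is given that way, about 69% of the day-28 window precedes randomisation and the treatment difference is attenuated

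*Protocol article*

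**What the plan says.** All references are to the protocol article.

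- **Outcomes, Primary outcome.** The PCL-5 is the only primary outcome. Its 20 items are described as asking how much the participant was "bothered by common PTSD symptoms in the past 3 months".
- **Assessment and collection of outcomes, and Table 2.** The PCL-5 is given at screening, day 0, days 7, 14 and 21, and day 28, which is the primary endpoint. In the text, "participants will return and be re-evaluated weekly on PTSD symptoms".
- **Trial allocation.** "subjects will complete all baseline assessments followed by a simple randomisation in a 1:1 ratio". Time on allocated treatment therefore starts at day 0.
- **Data analysis.** The arms are compared at week 4 with a two-sample t-test or Mann-Whitney test. Variables with several time points are also analysed with mixed-effects models.

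No section gives a shorter recall period for the PCL-5, or one that changes between screening, baseline and follow-up.

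**The concern.** The stated recall period is more than three times the length of the intervention and thirteen times the interval between visits. A woman who answers the day-28 form as described reports mainly on the time before she was randomised. Treatment cannot have affected that time, so including it shrinks the difference between arms.

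The stake is how a null result would be read. If the only primary outcome largely covers the pre-trial period, a small or absent difference could mean that exercise does not help, or that the scale could not register a four-week change at full size. The weekly trajectory suffers more, because adjacent scores refer to almost the same days.

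This is not detail that an article leaves to the full protocol. The article states the window, and that window does not fit its own schedule.

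**Working it through.** **Inputs from the article.** Recall window W: 3 months, taken as 91 days (13 weeks), with 84 to 92 days as the range. Visits at t = 7, 14, 21 and 28 days after randomisation. Target of 120 with 20% dropout (Sample size).

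**The plan's own figure.** The sample size is taken from earlier trials of 46 to 96 participants. 96 / (1 − 0.20) = 120, which reproduces the target and gives 96 / 2 = 48 analysed per arm. No effect size on the PCL-5 is stated, so 120 neither supports nor contradicts this point.

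**Share of the window before randomisation** = (W − t) / W, with W = 91:

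| Visit | Days before randomisation | Share |
|---|---|---|
| Day 7 | 84 / 91 | 92.3% |
| Day 14 | 77 / 91 | 84.6% |
| Day 21 | 70 / 91 | 76.9% |
| Day 28 | 63 / 91 | 69.2% |

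At day 28 the share is 66.7% for W = 84 and 69.6% for W = 92. Consecutive weekly windows share 91 − 7 = 84 of 91 days (92%).

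**How shorter windows would behave (assumed lengths).** A 7-day window has no pre-randomisation part at any follow-up visit. A window of 28 to 31 days has 0 to 10% at day 28, since (31 − 28) / 31 = 9.7%, but still 75 to 77% at day 7, since (28 − 7) / 28 = 75% and (31 − 7) / 31 = 77%.

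**Illustration of attenuation.** All inputs here are assumptions except the 48 per arm derived above. The true standardised difference is set at 0.578, the value that gives 80% power with 48 per arm at two-sided 5% (noncentral t). The SD is held fixed. The answer is treated as a weighted average of severity over 91 days.

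- Equal weights, full effect from day 1: retained share 28/91 = 0.308.
- Recency weights with half-life h, full effect from day 1: retained share (1 − 2^(−28/h)) / (1 − 2^(−91/h)). For h = 28 this is 0.500 / 0.895 = 0.56. For h = 14 it is 0.750 / 0.989 = 0.76.
- Benefit building linearly from zero at day 0 to its full size at day 28: the on-treatment days carry only part of the effect. With equal weights the retained share is 0.5 × 28/91 = 0.154.

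| Weighting of days | Retained, effect from day 1 | Measured difference (SD) | Power | Power, linear build-up |
|---|---|---|---|---|
| No attenuation | 100% | 0.58 | 80% | – |
| Half-life 14 days | 76% | 0.44 | 57% | 26% |
| Half-life 28 days | 56% | 0.32 | 35% | 14% |
| Equal over 91 days | 31% | 0.18 | 14% | 7% |

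**The case against.** **It may be only a slip in the description.** The sentence describes the instrument in general; it does not say which form is loaded in REDCap. The article has other slips of this kind: DSM-5 is misprinted in the same section, the DASS has 12 items in the outcomes and 21 in the abbreviations, and the Fitbit model differs between sections. This stands. A reader might infer that the trial is certainly collecting a diluted primary outcome, but the documents establish only that the description conflicts with the schedule. Everything about attenuation is conditional on the form matching the description.

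**People answer about how they feel now.** Recent weeks may well weigh more. It is therefore tempting, but wrong, to read 28/91 = 31% as a ceiling on the measured effect. It is the value under equal weighting, which nothing in the article supports, and recency weighting gives more. For the same reason, to say that the scale cannot measure a four-week change goes too far: it would measure it with attenuation. Even so, the 14-day half-life takes power from 80% to 57% in the illustration.

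**The SD would not stay fixed.** If answers averaged over three months, short-term variation within a woman would partly average out and the SD would fall, so the standardised effect would shrink somewhat less than shown. This is fair, and another reason to treat the power figures as illustrative. So is the 0.58 SD, which is back-solved from 96 analysed and is not a planning value.

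**Randomisation balances the pre-trial part.** This is correct: the consequence is lost sensitivity and does not favour either arm. The day 7 to 21 shares bear only on the additional mixed-model analysis; the week-4 comparison rests on the day-28 share.

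**Conclusion.** As written, the recall period of the only primary outcome does not fit a 28-day trial with weekly scoring, and nothing else in the article resolves it. The firm result is calendar arithmetic: 69% of the day-28 window lies before randomisation (67–70% over the plausible lengths of 3 months).

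If the form is given as described, the treatment difference is attenuated. How much depends on how women weight the days and how fast benefit appears, neither of which the article gives. Across the assumptions tried with an effect from day 1, 31% to 76% of the effect is retained; a gradual build-up gives less.

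The conflict has to be resolved whichever explanation is right, because it concerns the published definition of the primary outcome.

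**What to change.** 1. **Check the form.** State the recall period actually used at screening, baseline, the weekly visits and day 28.
2. **If it is shorter than 3 months,** correct the Primary outcome section. Do not read an early visit as a treatment effect where its window reaches back before day 0.
3. **If it is 3 months,** use for baseline and follow-up, in both arms, a window that at day 28 lies within the 28-day treatment period. If weekly scores are to be interpreted, it must also fit within the visit interval. A past-week form meets both conditions but is not the only choice for day 28. Keep the longer window for screening only.
4. **If the form changes mid-trial,** record the version each participant received. Let the treatment effect differ by version, through a treatment-by-version term or stratified estimates. A main effect for version is not enough, because the expected treatment difference itself depends on the window. State that results from the 3-month form are attenuated.

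**Cost.** Checking the form and correcting the text costs little. A change of form needs an ethics amendment and splits the primary outcome into two versions, because women have been enrolled since May 2024; each version-specific estimate then rests on fewer participants. Data collection is expected to run to May 2027, so if the 3-month form is in use, each further participant assessed on it adds to the attenuated part.
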